### Interventions

The acupuncture regimens were determined according to the clinical practice of acupuncture experts and literature on acupuncture treatment of AF [16, 17, 26, 27]. All acupuncture operations will be performed by professional acupuncturists who have obtained a Chinese medicine practitioner license with more than 3 years of clinical experience. Besides, all patients will receive relatively uniform post-ablation management after CA.

Before the study, all acupuncturists will be specially trained in the standardized operation procedure of acupuncture, including accurate positioning of acupoints, operational methods, and so on. Besides, brochures showing the information on the standardized operation in detail will be provided to the acupuncturists for reference. Within 3 months after CA (blanking period), patients will receive acupuncture treatment twice per week for weeks 1–6 and once per week for weeks 7–12 (18 sessions in total). Sterilized disposable steel needles (Hwato disposable acupuncture needle; Suzhou, Jiangsu, China) will be used in the treatment and in sizes of 0.30 mm × 25 mm or 0.30 mm × 40 mm. Standardized prescriptions will be used in the three groups. Bilateral *xinshu* (BL15), *neiguan* (PC6), and *shenmen* (HT7) will be selected in the SA group. Bilateral pohu (BL42), tianquan (PC2), and qingling (HT2) will be selected in the NSA group. The code and location of the acupoints are consistent with the WHO standards [28]. The exact locations of all acupoints are listed in Table 1 and marked in Fig. 2. The three non-acupoints chosen for the NA group are separated from known acupoints. The locations of non-acupoints are shown in Table 2 and also marked in Fig. 2.

**Table 1 Tab1:** Locations of acupoints for specific acupoints group and non-specific acupoints group

	Acupoint	Location
Specific acupoints	Xinshu (BL15)	In the upper back region, at the same level as the inferior border of the spinous process of the fifth thoracic vertebra (T5), 1.5 cun^a^ lateral to the posterior median line.
	Neiguan (PC6)	On the anterior aspect of the forearm, between the tendons of the palmaris longus and the flexor carpi radialis, 2 cun proximal to the palmar wrist crease.
	Shenmen (HT7)	On the anteromedial aspect of the wrist, radial to the flexor carpi ulnaris tendon, on the palmar wrist crease.
Non-specific acupoints	Pohu (BL42)	In the upper back region, at the same level as the inferior border of the spinous process of the third thoracic vertebra (T3), 3 cun lateral to the posterior median line.
	Tianquan (PC2)	On the anterior aspect of the arm, between the long head and short head of the biceps brachii muscle, 2 cun distal to the anterior axillary fold.
	Qingling (HT2)	On the medial aspect of the arm, just medial to the biceps brachii muscle, 3 cun superior to the cubital crease.

^a^1 cun (≈ 20 mm) is defined as the width of the interphalangeal joint of the patient’s thumb

**Fig. 2 Fig2:**
[figure not shown]
Locations of acupoints and non-acupoints

**Table 2 Tab2:** Locations of non-acupoints group

Non-acupoints	Location
NA1	In the middle of Shentang (BL44) and Tianzong (SI11) points
NA2	In the middle of Tianquan (PC2) and Qingling (HT2) points
NA3	In the middle of Quze (PC3) and Qingling (HT2) points

#### SA group

All four acupoints in this group are specific acupoints. Acupuncture is performed in a certain sequence of acupoints: BL15, PC6, and HT7. Firstly, BL15 will be punctured obliquely to a depth of 1.0–1.6 cm. Then, the needles will be stimulated (lift and thrust or twirl and rotate the needles) manually to achieve the Deqi sensation (the sensation including soreness, numbness, distention, or heaviness accompanied by acupuncture). The stimulation will continue for 1 min, and then the needles will be pulled out. Secondly, PC6 will be punctured perpendicularly 1.0–2.0 cm. HT7 will be punctured perpendicularly 0.6–1.0 cm. PC6 and HT7 are also stimulated to achieve Deqi. After that, needles will be retained in place for 30 min. 

#### NSA group

Non-specific acupoints are a group of acupoints that are not thought to have similar specific effects to specific acupoints. The nearby non-specific points belonging to the same meridians of the specific acupoints group for treatment were selected as in some previous studies [21, 22]. The sequence of acupuncture will be BL42, PC2, and HT2. BL42 will be punctured obliquely 1.0–1.6 cm using identical operation with BL15. PC2 will be punctured perpendicularly 2.0–3.0 cm. HT2 will be punctured perpendicularly 1.0–2.0 cm. The acupuncturist will use the same operation as PC6 and HT7 at PC2 and HT2 in the SA group.

#### NA group

Shallow puncture (2–3 mm in depth) will be performed without obtaining Deqi. It will be safe and not do any harm to the patients. Acupuncture will follow this sequence: NA1, NA2, NA3. Needles in NA2 and NA3 should be left for 30 min, whereas needles will not be retained in NA1.

#### Post-ablation management

Electrical cardioversion is allowed within 3 months after CA (blanking period). The blanking period refers to a period of 3 months after any form of cardiac ablation during which arrhythmias are not considered. Patients who experience AF recurrence after the blanking period will be allowed to start or resume AADs or undergo a repeat ablation. According to the guidelines of the ESC [6] and Chinese guidelines [29] for the management of AF, all patients will receive routine medication after CA. The drugs protocol includes anticoagulation (at least 8 weeks after CA), AADs (continued 3 months after CA), and proton pump inhibitor (4 weeks). Moreover, patients are required to keep a detailed record of their medication use, including name, duration, and dose.

### Outcomes

#### Primary outcome measurement

The primary outcome is the AF burden at 6 months after CA. AF burden will be measured by NS-SP-B-01 smart patch (Ensense Biomedical Technologies Co., Ltd., Shanghai, China). The smart patch will carry out continuous ambulatory electrocardiographic monitoring for 7 days. AF burden is expressed in the form of a percentage, which specifically refers to the proportion of time in AF within 7-days’ long for one patient in this study (range 0–100%). When the monitoring is complete, the patient will return the smart patch and the researchers can get the recordings. After the researcher transmits the recordings to the Ensense Company, the recordings will be analyzed by an appropriate algorithm. The results then will be reviewed by certified cardiac technicians to assure analysis quality and generate a report transmitted to the researchers.

#### Secondary outcome measurements

##### AF burden at 3 months after CA

AF burden at 3 months after CA will be measured by the same method as the primary outcome. This outcome is to evaluate whether acupuncture can reduce the duration of AF after treatment.

##### Time to AF recurrence

Recurrence of AF within 6 months after CA will be measured, and it is defined as any atrial tachyarrhythmia including AF/ atrial flutter/atrial tachycardia lasting 30 s or longer after the 3-month blanking period. Patients will be instructed to obtain 12-lead electrocardiograph (ECG) or 24 h Holter in order to verify the recurrence whenever they experience AF-related symptoms (palpitations, dyspnea, chest pain, etc.). Additionally, recurrence will be monitored via the smart patch regardless of the existence of symptoms at the end of 3 and 6 months. All researchers are required to receive training in the procedure of electrocardiographic monitoring and the use of the NS-SP-B-01 smart patch. They will then be responsible for explaining the use of the device to the patients.

##### Atrial Fibrillation Effect and Quality of Life Scale (AFEQT)

The AFEQT [30] is a questionnaire specially designed to assess the quality of life in atrial fibrillation patients. The assessment will take place at baseline and 3 and 6 months. A summary score and subscale scores in the following 3 domains: symptoms, daily activities, and treatment will be calculated. Summary and subscale scores range from 0 to 100 (complete to no AF-related disability).

##### Heart rate variability

Heart rate variability will be generated while monitoring AF burden with the smart patch to quantitatively evaluate the balance between the sympathetic and vagus nerves at 3 and 6 months.

##### Credibility and expectancy

A Credibility/Expectancy Questionnaire [31] will be used to measure the patients’ attitudes toward acupuncture before treatment.

##### Blinding assessment

Blind evaluation will be conducted in order to evaluate whether the blind method is successful. After treatments in weeks 6 and 12, all patients will be asked to guess whether the needles go deep or shallow layers in the acupuncture treatment they receive. Before the treatment, one or two doctors of each center will be in charge of recruiting the patients and gaining informed consent from them. The patients will be informed: “There are three different groups of acupuncture with three different acupoint selection schemes. You are equally likely to be assigned to all three groups, and previous studies have shown that all three methods were associated with positive outcomes in clinical studies.”

##### Others

They include the number of electrical cardioversion within the blanking period, the number of repeat CA after the blanking period, and the number of AF-related hospitalizations.

### Adverse events

Any adverse events and how they are dealt with will be recorded from baseline to 6 months. These adverse events specifically included bleeding, hematoma, fainting, severe pain, and local infection. If any serious adverse event occurs to the patient, which will be immediately reported to the primary investigator and all details will be recorded. The patient will be withdrawn from the trial.

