### Statistical analysis

Baseline characteristics will be summarized by the treatment group. Continuous variables will be described as mean ± standard deviations (normal distribution), or medians and interquartile ranges (non-normal distributions). Analysis of variance (ANOVA) or Kruskal-Wallis test (if normality is violated) will be applied in the comparison among three groups. Categorical variables will be described as frequency (percentage) and compared by *χ*^2^ test or Fisher’s exact test etc. As for the primary outcome, AF burden is expressed in the form of a percentage, which specifically refers to the proportion of time in AF within 7-days’ long for one patient in this study (range 0–100%). The null hypothesis that AF burden would be equivalent among the three arms (H0: effect of SA =effect of NSA = effect of NA) will be tested. The means of AF burden at 6 months of the three arms will be compared using ANOVA based on the preliminary assessment of the data distributions. If the ANOVA test among 3 arms is significant, the pairwise comparison will be performed by the least significant difference (LSD) test, and mean differences of pairwise comparison will be reported as effect measure. If AF burden is a skewed distribution, the data will be transformed to a normal distribution by corresponding methods for further comparison, and the same statistical analysis strategy will be adopted. The comparisons of AF recurrence between the three arms at 6 months will be performed based on a time-to-first-event analysis using the log-rank test. Kaplan-Meier cumulative AF recurrence rates will be calculated for each arm, with event or censoring times measured from the time of randomization. Hazard ratios (HRs) with associated 95% CIs will be derived using the Cox proportional hazards model.

All efficacy analyses will be based on the intention-to-treat principle. Missing data on the primary outcomes will be imputed by multiple imputations. An independent statistician who is blinded will conduct the statistical analysis using SAS 9.3. We will set a significance level of *P* < 0.05 (two-sided) without adjustment on account of the values considered explorative.

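### Withdrawing every patient from the trial after any serious adverse event, with no continued follow-up stated, conflicts with the intention-to-treat analysis

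*Protocol article*

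**What the plan says.** In the protocol article, the Adverse events section sets the rule in two consecutive sentences: "If any serious adverse event occurs to the patient, which will be immediately reported to the primary investigator and all details will be recorded", and then "The patient will be withdrawn from the trial". The same section sets the recording window, "Any adverse events and how they are dealt with will be recorded from baseline to 6 months", and gives examples, "These adverse events specifically included bleeding, hematoma, fainting, severe pain, and local infection". It does not define *serious*, does not require a relation to acupuncture, and does not distinguish leaving treatment from leaving follow-up.

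The Primary outcome measurement section says "The primary outcome is the AF burden at 6 months after CA", taken from a 7-day patch. The Statistical analysis section says "All efficacy analyses will be based on the intention-to-treat principle" and "Missing data on the primary outcomes will be imputed by multiple imputations".

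Under secondary outcomes, the section headed Others counts, besides cardioversions, "the number of repeat CA after the blanking period, and the number of AF-related hospitalizations". Post-ablation management permits repeat ablation once AF has recurred after the blanking period. Interventions ends the acupuncture course at week 12. Sample size sets 20 patients per arm, 60 in all.

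**The concern.** Intention to treat depends on following every randomised patient to the outcome, whatever happens after randomisation. The Adverse events section orders the opposite for patients with the most severe events, so the protocol itself creates missing data that could have been collected.

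Three things are at stake. First, the primary outcome would be missing for patients who left because of a serious health event, and that reason is probably related to their rhythm outcome. Second, safety observation would end at the first serious event, although safety is a stated aim and adverse events are meant to be recorded for 6 months. Third, the pilot is to supply the figures for sizing a larger trial. If patients with high burden leave more often, the mean and spread carried forward would be distorted.

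**Working it through.** **1. Can the rule mean only that needling stops?** Adverse events are recorded to month 6, and needling ends at week 12. For a serious event between week 12 and month 6 there is no study treatment left to stop. In that window, withdrawal can only mean the end of follow-up, and the window leads directly to the 6-month patch.

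**2. What is lost and what is kept?** The triggering event is kept, because its details are to be recorded. A recurrence already documented stays in the time-to-first-event analysis. What is lost comes after the event: the 6-month AF burden, AFEQT, heart rate variability, later admissions and ablations, and later adverse events.

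**3. How many patients?** The plan's figure reproduces: 3 × 20 = 60. One loss is 1/20 = 5% of an arm. The article gives no rate *s* of serious adverse events, so the rates below are assumptions. Retained = 60 × (1 − *s*).

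| Assumed *s* | Retained of 60 | Per arm (if equal) |
|---|---|---|
| 5% | 57 | 19 |
| 10% | 54 | 18 |
| 20% | 48 | 16 |
| 30% | 42 | 14 |

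**4. If AF-related admission or repeat ablation counts as serious.** This step is conditional. Let *r* be the recurrence rate, *h* the share of patients with recurrence who are withdrawn, and *b* the mean burden in patients with recurrence. Take burden as 0 without recurrence, and assume that only patients with recurrence are withdrawn, with the same mean burden as those who stay. The Background section gives one-year success of 45–60% for persistent AF, so *r* = 40–55%. That is only a proxy for 6 months. The values of *h* are assumptions.

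- Full mean: *rb*
- Mean in patients still observed: *r*(1 − *h*)*b* / (1 − *rh*)
- Ratio of the two: (1 − *h*) / (1 − *rh*), which does not depend on *b*
- Primary outcomes lost: 60*rh*

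| *r* | *h* | Lost of 60 | Ratio | Relative shortfall |
|---|---|---|---|---|
| 0.40 | 0.10 | 2.4 | 0.90/0.96 | 6% |
| 0.55 | 0.10 | 3.3 | 0.90/0.945 | 5% |
| 0.40 | 0.25 | 6.0 | 0.75/0.90 | 17% |
| 0.55 | 0.25 | 8.25 | 0.75/0.8625 | 13% |
| 0.40 | 0.50 | 12.0 | 0.50/0.80 | 38% |
| 0.55 | 0.50 | 16.5 | 0.50/0.725 | 31% |

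This is the shortfall in mean burden that imputation would have to make good. It can do so fully only if its model carries the reason for withdrawal.

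**5. Does this bias the comparison between arms?** Not necessarily. If *r* and *h* are equal in two arms, both means shift equally and the difference is unaffected. If *r* = 0.40 in both arms but *h* is 0.10 in one and 0.25 in the other, the observed means are 0.36*b*/0.96 = 0.375*b* and 0.30*b*/0.90 = 0.333*b*. A true difference of 0 then appears as 0.042*b* (1.7 percentage points at *b* = 40) in favour of the arm with more withdrawals. Exchanging the two values of *h* reverses the sign. The direction cannot be known in advance.

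**The case against.** The strongest defence has four parts.

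- The article does not exclude withdrawn patients from the analysis, and multiple imputation is planned for the primary outcome. All 60 can therefore be analysed as randomised.
- The adverse events named are of the kind needling causes. Repeat ablation is permitted management, and both repeat ablation and AF-related admission are counted as outcomes. The authors may never have meant these to trigger withdrawal.
- *Withdrawn* may be loose wording for stopping acupuncture.
- This is an exploratory pilot with unadjusted P values.

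The first part stands as far as it goes. A reader might infer that the rule breaks the intention-to-treat analysis outright, and the document does not support that. It does make the analysis depend on imputing data that need not have been missing.

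The second part also stands. A reader might infer that patients with AF admission or repeat ablation are removed from the outcomes, or that admissions cannot exceed one per patient. Both need a definition of *serious* that the article does not give, and even then the triggering event is still counted.

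The third part fails for events after week 12, as step 1 shows. The fourth affects how much weight any P value bears, but not the value of complete data in a pilot meant to assess safety and feed a sample-size calculation.

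A reader might also infer that the rule would erase a real effect. Suppose 25% of the NA arm and 10% of the SA arm are admitted, with mean burden 60% if admitted and 10% if not. The true means are 0.25 × 60 + 0.75 × 10 = 22.5 and 0.10 × 60 + 0.90 × 10 = 15, a difference of −7.5 points. Dropping all admitted patients leaves 10 against 10. The zero is built in, because the example gives non-admitted patients the same mean in both arms. Nor can one say that missing values would be imputed only from patients who stayed well: retained patients include those with recurrence but no admission, and no imputation model is given.

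**Conclusion.** The point holds in this form: the rule on withdrawal after any serious adverse event conflicts with the intention-to-treat statement, because it ends follow-up whatever the cause of the event and through month 6. This follows from the text alone and needs no assumption about rates.

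Its size is not known. Each loss is 5% of an arm. The retained numbers of 57 to 42 rest on assumed event rates of 5% to 30%. The 5% to 38% relative shortfall in observed mean burden rests further on AF admission or repeat ablation counting as serious, on a one-year recurrence range used for 6 months, on assumed withdrawal shares of 10% to 50%, and on the simplifications listed in step 4. No claim can be made about the size or direction of bias in the difference between arms.

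It should be corrected now. The Trial status section says that recruitment is under way, and a 6-month recording that was not made cannot be recovered later.

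**What to change.** Reconcile the Adverse events and Statistical analysis sections by separating two decisions: stopping study treatment and stopping follow-up. The first is a clinical decision, and nothing is proposed on it here. For the second, wording such as this would serve:

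*Whatever is decided about study treatment after a serious adverse event, the 3- and 6-month patch recordings, AFEQT, hospitalisation, repeat-ablation and adverse-event data continue to be collected for all randomised patients, unless the patient withdraws consent to follow-up.*

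Keep multiple imputation for data that cannot be obtained. State also whether AF-related admission and repeat ablation are handled as serious adverse events, as outcomes, or as both, so that the four centres apply the rule alike.

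The cost is a short protocol amendment. The visits, questionnaires and patches are already planned for every patient.

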### Data management

Detailed time points of outcome assessments are provided in Fig. 3. Throughout this study, the data of all patients will be recorded on the case report form (CRF). When the forms are completed, the data will be entered into the Excel spreadsheet independently by two researchers. There will be a data manager to compare the two sets of data. If any differences are found, they will be corrected according to the original CRFs. All documents related to the research, including the paper files and electronic documents, will be well preserved for no less than 5 years after publication. The first author or corresponding author will provide the original data if anyone puts forward questions about the published data. It will be protected and never be disclosed that the patients’ personal privacy information includes name, gender, age, address, and telephone number. The ethics committee of Beijing University of Chinese medicine will audit trial conduct every 12 months.

**Fig. 3 Fig3:**
[figure not shown]
Schedule of enrollment, intervention, and assessments (SPIRIT figure). AF, atrial fibrillation; AFEQT, Atrial Fibrillation Effect on Quality of Life

### Sample size

The purpose of this pilot study is to evaluate the efficacy and safety of acupuncture in the treatment of AF and the feasibility for a further large-scale clinical trial. We did not find a suitable reference to calculate the sample size, but a minimum sample size of the clinical trial with 20 patients per group is used instead [32]. A total of 60 patients will be randomly assigned equally to SA, NSA, or NA group. This trial will provide data for sample size calculations of a future large-scale RCT.

### Statistical analysis

Baseline characteristics will be summarized by the treatment group. Continuous variables will be described as mean ± standard deviations (normal distribution), or medians and interquartile ranges (non-normal distributions). Analysis of variance (ANOVA) or Kruskal-Wallis test (if normality is violated) will be applied in the comparison among three groups. Categorical variables will be described as frequency (percentage) and compared by *χ*^2^ test or Fisher’s exact test etc. As for the primary outcome, AF burden is expressed in the form of a percentage, which specifically refers to the proportion of time in AF within 7-days’ long for one patient in this study (range 0–100%). The null hypothesis that AF burden would be equivalent among the three arms (H0: effect of SA =effect of NSA = effect of NA) will be tested. The means of AF burden at 6 months of the three arms will be compared using ANOVA based on the preliminary assessment of the data distributions. If the ANOVA test among 3 arms is significant, the pairwise comparison will be performed by the least significant difference (LSD) test, and mean differences of pairwise comparison will be reported as effect measure. If AF burden is a skewed distribution, the data will be transformed to a normal distribution by corresponding methods for further comparison, and the same statistical analysis strategy will be adopted. The comparisons of AF recurrence between the three arms at 6 months will be performed based on a time-to-first-event analysis using the log-rank test. Kaplan-Meier cumulative AF recurrence rates will be calculated for each arm, with event or censoring times measured from the time of randomization. Hazard ratios (HRs) with associated 95% CIs will be derived using the Cox proportional hazards model.

All efficacy analyses will be based on the intention-to-treat principle. Missing data on the primary outcomes will be imputed by multiple imputations. An independent statistician who is blinded will conduct the statistical analysis using SAS 9.3. We will set a significance level of *P* < 0.05 (two-sided) without adjustment on account of the values considered explorative.

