## Discussion

AF is one of the leading causes of stroke and cardiovascular diseases. It is of great significance to find combination therapy to maintain sinus rhythm. This pilot study is designed to evaluate the feasibility, efficacy, and safety of acupuncture in reducing AF burden in a specific group of patients with persistent AF after CA.

Previously, an RCT was conducted to prevent AF recurrence after electrical cardioversion with acupuncture in persistent AF [16]. AF was detected only by 12-lead ECG, which could underestimate the recurrence rate of AF. Another study was designed to determine whether acupuncture could reduce the early recurrences of AF after CA in persistent AF [17]. In the study, the measured recurrence rate of AF was the early recurrence rate within the blanking period, and the long-term prognosis was not studied, which is a more appropriate endpoint. In addition, neither of the two studies evaluated the quality of life that is of great concern in AF patients [33, 34].

The recurrence rate is often used as the primary outcome in clinical trials on AF. However, recurrence is a binary concept, reflecting only the presence and absence. In contrast, AF burden is the primary outcome of our study, which can represent the quantity or amount of AF that one person has. It helps analyze the therapeutic efficacy quantitatively. The AF recurrence after the blanking period will be set as a significant secondary outcome in our study. We will both use 12-lead ECG and 24-h Holter during the monitoring, which may ensure AF recurrence detected in time. Moreover, we will evaluate the quality of life through AFEQT. The control group is the NA group in which shallow insertion at non-acupoint is a kind of sham treatment of acupuncture. Shallow insertion in non-acupoints applied as a sham control was established in the light of two literature reviews [35, 36]. In addition, this placebo control has been verified to be successful in blinding Chinese patients suffering from postprandial distress syndrome [37] and chronic severe functional constipation [38]. Compared with a blank control group, sham acupuncture can largely eliminate the interference of non-specific effects. We will choose the acupoints selection scheme with better efficacy through the comparison between group SA and group NSA, which will be applied in the future large-scale RCT.

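### Pairwise differences in AF burden are to be reported only after a significant three-arm ANOVA, although one stated aim and the choice of acupoint scheme need them whatever the p-value

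*Protocol article*

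**What the plan says.** The primary analysis in the Statistical analysis section starts with an omnibus test: "The means of AF burden at 6 months of the three arms will be compared using ANOVA". It continues that, if this ANOVA "is significant, the pairwise comparison will be performed by the least significant difference (LSD) test". The rest of that sentence names the pairwise mean differences as the effect measure to be reported, so testing and reporting hang on the same condition. If AF burden is skewed, the data are transformed and the same sequence is followed. The section sets no other rule for pairwise estimates of AF burden. The hazard ratios for recurrence, in contrast, are planned with 95% CIs and without any condition. On the error rate the section says: "We will set a significance level of *P* < 0.05 (two-sided) without adjustment on account of the values considered explorative".

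Three other places say what the results are for:
- The third aim, at the end of the Background, is a pairwise question: SA against NSA and SA against NA.
- The Discussion says: "We will choose the acupoints selection scheme with better efficacy through the comparison between group SA and group NSA". That scheme then goes into the large trial.
- The Sample size section says: "This trial will provide data for sample size calculations of a future large-scale RCT".

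**The concern.** Choosing between SA and NSA, and judging SA against NA, are estimation tasks. They need the size of each difference and how uncertain it is. Under the rule as written, a non-significant ANOVA leaves the plan without any AF-burden contrast to report, while the Discussion promises a choice made through one of those contrasts. Both statements cannot be followed in that case. When the ANOVA is significant, the reported contrasts have passed a significance filter, so over repeated pilots they are too large on average. With 20 patients per arm, neither effect is negligible unless the true difference is large. The exploratory label does not help, because exploratory work relies on estimates with intervals more than on tests.

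**Working it through.** **Inputs from the protocol article.** 20 per arm ("a minimum sample size of the clinical trial with 20 patients per group is used instead"), three arms, 3 x 20 = 60 in total, two-sided 0.05 without adjustment. There is no power calculation to reproduce: the Sample size section gives no effect size, SD or power.

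**Assumptions.** Normal data with a common SD. True SA-NA difference d in SD units. NSA lies either midway between SA and NA or equal to NA.

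**Step 1: chance that the ANOVA is significant.** The test is F(2,57) with critical value 3.16. The noncentrality is 20 x the sum of squared deviations of the arm means from their average.
- NSA midway: 20 x 2 x (d/2)^2 = 10 d^2.
- NSA equal to NA: 20 x (2/3) d^2 = 13.33 d^2.

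At d = 0.5 these are 2.5 and 3.33. The noncentral F distribution gives:

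| True SA-NA (SD) | NSA midway | NSA = NA |
|---|---|---|
| 0.3 | 12.0% | 14.5% |
| 0.5 | 26.1% | 33.7% |
| 0.8 | 58.9% | 72.3% |
| 1.0 | 79.3% | 90.0% |

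The chance reaches 50% at d = 0.72 (NSA midway) or 0.63 (NSA = NA). With no true difference it is 5%.

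**Step 2: size of the SA-NA estimate given a significant ANOVA.** Simulated mean divided by the truth (60,000 trials per scenario):

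| True SA-NA (SD) | NSA midway | NSA = NA |
|---|---|---|
| 0.3 | 2.4 | 2.2 |
| 0.5 | 1.7 (mean 0.85) | 1.5 (mean 0.77) |
| 0.8 | 1.25 | 1.15 |
| 1.0 | 1.11 | 1.05 |

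For SA-NSA with NSA midway and d = 0.5, the truth is 0.25 and the mean reported value is about 0.43.

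**Step 3: sensitivity to the shape of AF burden.** Many patients may have a burden of zero, so the check was repeated on untransformed zero-inflated data. Recurrence in the NA arm was assumed to be 40-55%, scaled from the 45-60% one-year success rate in the Background. If SA cuts recurrence by a quarter or a half, the ANOVA is significant in 6-42% of trials and the exaggeration is 1.4-3.4 times. With a three-quarter cut it is significant in 25-84%.

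**Step 4: what unconditional reporting gives.** An estimate is then available in every pilot and is unbiased for normal data (simulated mean 0.499 for a true 0.50). The half-width of its 95% CI is t(0.975, 57) x sqrt(2/20) = 2.002 x 0.316 = 0.63 SD.

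**The case against.** Several points on the other side stand.

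- An omnibus test before LSD comparisons is a legitimate testing procedure for three groups. The fault lies only in tying estimation to it.
- The information is not lost. The arm means and the pooled SD come out of the ANOVA whatever its p-value, and the Data Availability statement promises individual data. Crude differences could be derived. But the plan does not commit to reporting them, and subtracting crude means would not reflect the planned multiple imputation.
- The Discussion does not say that the choice of scheme rests on AF burden, and the recurrence hazard ratios are reported unconditionally. So it does not follow that there would be no basis at all for a choice. AF burden is nevertheless the primary outcome.
- A full analysis plan may tabulate the contrasts anyway. That would remove the problem in practice, but the article states a rule, and that rule conflicts with the article's own uses.

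A reader might infer that the pilot cannot serve its purpose. The documents do not support this: the SD, the Kaplan-Meier recurrence rates per arm and the hazard ratios are all available for planning the next trial.

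A reader might also infer that the main trial will be undersized. At 90% power, n per arm = 2 x (1.96 + 1.2816)^2 / d^2. That is about 84 for a true 0.5 SD and about 29 for the filtered 0.85 SD, and 29 per arm has about 48% power at 0.5 SD. The figures are only illustrative, because nowhere does the article say that the sponsor will plan on the filtered point estimate. Unconditional reporting would not change the estimate in any one pilot with a significant ANOVA either. It only stops the result from deciding whether an estimate appears.

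**Conclusion.** The point holds as a conflict between a stated reporting rule and stated uses, limited to the primary outcome. Its size depends on a true effect that the article does not give. Saying that the pilot will usually report no contrast is right only for true SA-NA differences below about 0.63-0.72 SD, including no effect. At 0.8 SD, 59-72% of pilots would report one. Exaggeration is material at 0.5 SD and below and minor at 1 SD. These figures assume normal data with complete follow-up of 20 per arm; the zero-inflated check points the same way but over a wide range. The weight is that of a cheap improvement, not a must-fix.

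**What to change.** In the Statistical analysis section, state that the SA-NA, SA-NSA and NSA-NA differences in AF burden at 6 months are estimated and reported with 95% CIs regardless of the ANOVA result, and that the ANOVA condition applies only to pairwise p-values. In the Discussion, state that the choice of scheme rests on the SA-NSA estimate and its CI.

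For the next trial's sample size, it is sensible to take variability and event rates from the pilot and the target difference from clinical relevance. Using an upper 80% confidence limit for the SD (about 1.09 times the estimate on 57 degrees of freedom) is optional.

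The cost is wording and a little more analysis, with no extra patients, visits or data. The downside is that wide intervals, about 0.63 SD either side, will be on display. With 20 per arm, that is an honest picture of what the pilot can show.
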